## Methods: participants, interventions, and outcomes

### Study setting {9}

This study will be conducted at the Department of Anesthesiology and Critical Care at All India Institute of Medical Sciences, Bhubaneswar, Odisha, India. AIIMS Bhubaneswar is a 900-bed tertiary care academic hospital, a designated center of national importance. It runs graduate and post-graduate training courses for a large number of medical and surgical specializations. The study is planned in the main operation theater complex with 25 operation theaters spread over four floors. Annually, more than 12,000 surgeries take place under general anesthesia.

### Eligibility criteria {10}

The participants included in the study will be:
i.Patient: Adult patients (age > 18 years) with ASA I to II functional status undergoing elective/emergency surgical procedures under general anesthesia who can understand and provide valid consent for the procedure. The exclusion criteria will be patients less than 18 years of age, American Society of Anesthesiologists (ASA) > 2 functional status, patients having Cormack Lehane (CL) grading more than 2 on direct laryngoscopy, use of airway adjuvants, and refusal to give consent for the study.ii.Intubator: Intervention (intubation) will be performed by trainee anesthesia residents who have less than 18 months of experience. As a part of the curriculum, training in the theory of airway management and mannikin intubations will ensure that all the trainees have experience of a minimum of 40 intubations on mannikins or patients. A consultant anesthetist will supervise all intubations per protocol.iii.Procedure: All procedures will be video recorded from the time patient is positioned after induction, and the laryngoscope is asked for, to after confirmation of correct tube position (this may be visual, auscultatory, or EtCO2 guided). Procedures where the trainee deviates from the methodology, improper table position, CL grade found > 2, use of a bougie, stellate, or other airway adjuncts, or take-over by the consultant (unanticipated difficult airway), will be video recorded but excluded from the analysis. This will reduce confounding the time to intubation due to poor visualization of the laryngeal inlet.

A few cases will be tried with a Go-Pro camera, hoping to ascertain data for the exact laryngoscopy view (with the understanding that the visual axis of the camera will not be identical to the LEI, and the forehead mounted camera might make the process more cumbersome for the trainee).

#### Dropout criteria

Any change in grip after holding the ETT, giving backward-upward-right-posterior pressure (BURP) to the larynx after holding ETT, or manipulation of the ETT like changing the curvature of the tube or rotating it by 180° will be video recorded but will be excluded from the final analysis. If any video has a conflict of opinion between the assessors regarding time to intubation or method of intubation, it will be excluded from the final analysis.

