### Criteria for discontinuing or modifying allocated interventions {11b}

If the intubator cannot intubate at the given tube mark, he will be allowed to change the site of grip—the site change will be noted from the video. If he/she still fails, the consultant can take over.

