### Outcomes {12}

Primary outcome measures: time to intubation (TTI) in both groups. The TTI will be calculated from holding the ET to removing the laryngoscope—after declaring a tube passed “under vision.” The frame has been chosen to reduce bias due to laryngoscopy problems or delay due to attaching the circuits and ventilating till capnographic confirmation of correct tube position. The primary outcome will be described in seconds.

Secondary outcome measures assessed will be first-pass intubation success rate; intubation difficulty scores (IDS) [6]; ease of the intubation assessed by the intubator, faculty, and a blinded assessor unrelated to the study on the Likert scale (0—very easy to 5—extremely difficult); and incidence of complications (bleeding or sore throat) in each group. The IDS comprises of attempt (in no), additional operators (if any, then in no), alternative technique: stylet/bougie, Cormack Lehane grading (CL grade: I/II/III/IV), lifting force: normal (0)/increased (1), external laryngeal pressure required during insertion of the tube: no (0)/yes (1), and position of vocal cords: abducted (0)/adducted (1).

Assessments from the video footage: These assessments will be done by two different anesthesiologists independently. The mean values will be used for analysis after disputes/disagreements (if any) are settled by a third person not belonging to the research team. This will reduce bias due to possible errors in time calculations.

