### Statistical methods

#### Statistical methods for primary and secondary outcomes {20a}

A researcher blinded to the group allocation will perform the statistical analysis of all randomized patients using the SPSS for Windows software (ver. 26.0; SPSS Inc., Chicago, IL, USA) on completion of the study.

Flowchart

For presenting the demographic data, the categorical data (like gender, SA status, gender) will be presented as a percentage of the total, while the quantitative data will be presented as means or medians with standard deviations or interquartile range. The data will be tabulated with standardized differences reported between groups.

The primary outcome will be described in seconds. The descriptive statistics that will be used is a standardized difference of means or proportions accordingly. All the secondary outcomes data, namely time to intubation and the IDS, are quantitative and will first undergo a normality test either the Shapiro-Wilk test or the Kolmogorov-Smirnov test to check the normality of the quantitative variables’ distribution. After this, the Mann-Whitney *U* test or independent *t*-test will be used, depending on whether the data is parametric or non-parametric, including the primary outcome variables. Accordingly, the data will be represented as mean with standard deviation or median with interquartile range.

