### Methods in analysis to handle protocol non-adherence and any statistical methods to handle missing data {20c}

Sensitivity analysis will be done to handle the missing data. Missing data will be handled with multiple imputations. Per-protocol and ITT analyses will both be done.

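### Randomised intubations are excluded for post-allocation events that the allocated grip can cause, in conflict with the all-randomised and ITT statements, and no primary analysis set is named

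*Protocol article*

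**What the plan says.** Two sections of the protocol article remove intubations from the analysis after randomisation.

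- *Dropout criteria*: "Any change in grip after holding the ETT, giving backward-upward-right-posterior pressure (BURP) to the larynx after holding ETT", and manipulation of the tube such as reshaping or a 180° turn, "will be video recorded but will be excluded from the final analysis".
- *Eligibility criteria {10}*, under Procedure: deviation from the methodology, poor table position, CL grade above 2, a bougie or other adjunct, "or take-over by the consultant (unanticipated difficult airway), will be video recorded but excluded from the analysis".

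Other sections describe some of the same events as permitted steps. *Criteria for discontinuing or modifying allocated interventions {11b}* states: "If the intubator cannot intubate at the given tube mark, he will be allowed to change the site of grip". If that also fails, the consultant can take over. *Technique* lets the faculty member approve a change of method, to be documented from the video. *Endotracheal tube* bars a stylet or bougie only on the first attempt.

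On the analysis population, *Statistical methods {20a}* says that a blinded researcher "will perform the statistical analysis of all randomized patients", and section {20c} says "Per-protocol and ITT analyses will both be done". Neither names the primary set, and neither exclusion rule is tied to one of the two analyses.

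**The concern.** The envelope is selected once the patient is in theatre and the checklist is done (*Personnel*), so every one of these events follows allocation. The tube is handed over only after an optimal view is confirmed (*Technique*). Grip change, pressure after holding the tube, and tube manipulation therefore also follow the start of the allocated grip. Adjunct use and take-over can do so too.

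The rationale in *Background {6a}* is that grip site alters the view and the ease of guiding the tube. If that is right, these events should be more frequent in one arm, and excluding them selects patients differently by arm. TTI would then be compared between groups that randomisation no longer balances.

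The secondary outcomes suffer as well. The IDS scores several of the events that cause exclusion, and first-pass success and complications lose the rescued or most manipulated airways. The *Sample size {14}* section justifies its target difference by the extra manipulation and trauma that a longer TTI implies. The exclusions remove intubations with that extra manipulation.

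**Working it through.** **1. The passages side by side.** {20a} (all randomised patients), {20c} (both ITT and per-protocol) and the two unconditional exclusion rules cannot all be followed as written. Section {11b} gives the causal chain: failure at the mark, then grip change, then possible take-over. The reason given in {10}, confounding by poor visualisation of the laryngeal inlet, does not cover events after a good view has been confirmed.

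**2. IDS items.** *Outcomes {12}* lists seven: attempts, additional operators, alternative technique, CL grade, lifting force, external laryngeal pressure during insertion, and vocal cord position. Additional operators (take-over), alternative technique (stylet or bougie) and external pressure (BURP) coincide with exclusion events. So three of seven are essentially zero in the retained set.

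**3. Effect on TTI.** The protocol has no figure to reproduce here, because it gives no exclusion rates. The following is illustration.

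Inputs from *Sample size {14}*: mean 8.83 s, SD 4.07 s, 180 per arm, 20% difference (0.2 × 8.83 = 1.766 s). Assumptions: log-normal times; one arm slower by a factor of 1.2; deletion of cases above a time cut-off, standing in for the excluded events.

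- σ = √ln(1 + (4.07/8.83)²) = 0.439; μ = ln 8.83 − σ²/2 = 2.082; slower arm μ + ln 1.2.
- Retained mean below cut-off c: mean × Φ(z − σ)/Φ(z), with z = (ln c − μ)/σ.
- Power: Φ(difference/SE − 1.96). With no deletion, SE = √((4.07² + 4.884²)/180) = 0.474, and 1.766/0.474 − 1.96 = 1.77, so power is 0.96.
- Worked row, c at the faster arm's 90th percentile (14.07 s): faster arm 8.83 × 0.800/0.900 = 7.85 s; slower arm 10.596 × 0.665/0.807 = 8.74 s; difference 0.89 s.

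| Cut-off (percentile of faster arm) | Dropped, faster vs slower arm | Retained difference | Power |
|---|---|---|---|
| none | 0% vs 0% | 1.77 s | 0.96 |
| 95th | 5% vs 11% | 1.11 s | 0.89 |
| 90th | 10% vs 19% | 0.89 s | 0.82 |
| 80th | 20% vs 33.5% | 0.64 s | 0.67 |

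If only half of the cases above each cut-off are removed, simulation gives 1.48, 1.41 and 1.39 s with power 0.94, 0.91 and 0.89. The closed form gives 1.47, 1.40 and 1.39 s with 0.93, 0.91 and 0.88.

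**4. No true difference.** Both arms have the same distribution, but the slowest cases are dropped at unequal rates. Retained means are 8.24 s (5% dropped), 7.85 s (10%), 7.53 s (15%) and 7.25 s (20%).

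- 5% vs 10%: false difference 0.38 s
- 5% vs 15%: 0.70 s
- 10% vs 20%: 0.61 s

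In each case the arm with more exclusions looks faster.

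**5. Loss allowance.** The allowance of about 20% on 180 per arm (36 patients, leaving 144) addresses numbers only. It does nothing about unequal selection.

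**The case against.** The strongest reply is that an ITT analysis is planned and its raw material is collected: excluded cases are still filmed, and changes of site and of method are recorded. The two exclusion lists may be an unlabelled definition of the per-protocol set. *Trial design {8}* also calls this an equivalence trial, where a per-protocol analysis normally carries weight. This reading is plausible, but the text does not state it. Both rules refer to the analysis without qualification, and the sample size rests on a two-sided equality test. What stands is that the documents contradict each other; they do not show that the ITT analysis has been abandoned.

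Several stronger readings are tempting and not supported.

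- *The rule must shrink the TTI difference.* It may do so, but step 4 shows that it can also create one. Without exclusion rates by arm, the direction is unknown.
- *Every excluded event is caused by the grip.* Adjunct use and take-over can precede handover, and {10} associates take-over with an unanticipated difficult airway. They can be consequences of the grip, but need not be.
- *CL III/IV is a fourth lost IDS item.* A CL grade above 2 is found before the tube is held, so the grip cannot cause it; excluding it is a stated limit on the population. Attempts, lifting force and cord position can still vary, so difficulty is not wholly removed.
- *Multiple imputation would turn failures into ordinary successes.* Section {20c} imputes missing data, and nothing says that failed or excluded cases count as missing.
- *Power is badly damaged.* Under half-deletion it stays above the planned 85%. The excluded events are also not durations, so the time cut-offs are a proxy.

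**Conclusion.** The point holds in this form: post-allocation exclusions that can depend on the allocated grip apply without limit to a per-protocol set, contradict {20a} and {20c}, and leave the primary set undefined. If followed, they give a selected comparison of the primary outcome.

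The size is conditional. Under the log-normal and time-cut-off assumptions, a true 1.77 s difference becomes 0.64–1.11 s with full deletion of slow cases and 1.39–1.48 s with half-deletion, where power stays at about 0.9. A null effect becomes a false 0.38–0.70 s when 5–10% of one arm and 10–20% of the other are dropped. Since no exclusion rates are given, neither the size nor the direction in this trial can be stated. The loss of three IDS items, and of rescued cases from first-pass success and complications, follows from the text and needs no such assumption.

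**What to change.** Reconcile *Eligibility criteria {10}* and *Dropout criteria* with {20a} and {20c}:

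1. Define the primary set as all randomised patients handed the marked tube after a confirmed CL 1–2 view, analysed as randomised. Include cases with grip change, BURP, tube manipulation, adjunct use or take-over after handover.
2. Measure TTI to final placement. Give take-over or failure the worst rank, and fix Mann-Whitney as the primary test. A single rule of this kind fits a test already named in {20a}.
3. Analyse first-pass success, IDS and complications in the same set.
4. Confine the post-handover exclusions to the per-protocol analysis already planned.
5. Keep the CL > 2 exclusion if wished, since it is made before handover. Keep the marked tube out of the intubator's sight until the view is declared, so that this exclusion cannot depend on allocation.

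The change should be settled before results by arm are examined, and the interim analysis after 120 cases should use the same set.

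The cost is mainly protocol and analysis-plan wording, because the excluded cases are already to be filmed. There are two real downsides. TTI is likely to be more variable than the pilot SD of 4.07 s, and the primary comparison becomes rank-based, so the sample-size statement, which rests on a comparison of means, needs to be revisited.

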##### Position

The head position will be optimized to get the best possible view of the vocal cords. The “sniffing position” that aligns the oral, pharyngeal, and laryngeal axes will be achieved by elevating the patient’s head, extending the head at the neck, and aligning the ears horizontally with the sternal notch. In morbidly obese patients, rolls will be utilized [2]. The operating table’s position will be at the height of the intubator’s xiphoid process and her/his eyes about 1 foot (∼30 cm) above the patient’s face to provide proper angles and distances for laryngoscopy [5]. If the table position is not “exact” (in the videography), but the intubator has declared a CL grade 1 or 2 view, the procedure will be considered adequate as the head and neck position has been considered less critical for a successful LEI [4].

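### The protocol both excludes and adjudicates videos on which the two assessors disagree about time to intubation; one rule must go, and the exclusion is the wrong one to keep

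*Protocol article*

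**What the plan says.** TTI is defined under Outcomes {12}: "The TTI will be calculated from holding the ET to removing the laryngoscope". It is read from video, and "These assessments will be done by two different anesthesiologists independently".

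Two rules cover the case where the readers differ:

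- **Dropout criteria:** "If any video has a conflict of opinion between the assessors regarding time to intubation or method of intubation, it will be excluded"; such a video is left out of the final analysis.
- **Outcomes {12}:** "The mean values will be used for analysis after disputes/disagreements (if any) are settled by a third person not belonging to the research team".

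Two further statements fix who is analysed. Statistical methods {20a} promises "statistical analysis of all randomized patients using the SPSS for Windows software". The section on non-adherence and missing data {20c} adds "Per-protocol and ITT analyses will both be done", with multiple imputation for missing data.

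**The concern.** A dispute over TTI is one event with two prescribed outcomes. Under one rule the randomized patient leaves the final analysis; under the other the patient stays, with an adjudicated value. The exclusion sentence is not limited to disputes that the third person cannot settle, nor to the per-protocol set. Neither section says how many seconds apart two readings must be to count as a conflict.

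The exclusion is also of an awkward kind. It is applied after randomization, and its trigger is the measurement of the primary outcome. If ambiguous videos tend to be the longer ones, the rule trims the slow tail, and trims it more in the slower arm. The comparison of TTI would then no longer be a comparison of the randomized groups.

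**Working it through.** **1. The texts side by side.**

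| Question | Dropout criteria | Outcomes {12} |
|---|---|---|
| Trigger | Conflict on TTI or on method | Disputes or disagreements in the video assessments |
| Who resolves it | Nobody | A third person from outside the research team |
| Patient in the final analysis? | No | Yes, with mean values |
| Tolerance in seconds | None given | None given |

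For TTI and method the triggers overlap and the outcomes are opposite. Disagreements on the difficulty score or on ease fall only under Outcomes {12}. The exclusion also does not fit an analysis of all randomized patients. Nor is a disputed TTI a missing value that needs imputation, since two readings of it exist.

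**2. Loss of numbers.** The article states no disagreement rate, so there is no figure of its own to reproduce. Planned recruitment is 180 per group against a stated requirement of 149, an allowance of 180 − 149 = 31 per group. If disputed videos are excluded, then at assumed rates:

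- 5%: 180 × 0.95 = 171 per group
- 10%: 180 × 0.90 = 162 per group
- 20%: 180 × 0.80 = 144 per group, below 149 before any other loss

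Under adjudication none of the allowance is spent on disagreement.

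**3. Possible effect on the estimate (hypothetical).** Sample size {14} gives a mean of 8.83 s and an SD of 4.07 s, and treats a 20% difference as clinically significant: 0.20 × 8.83 = 1.77 s. Assume lognormal TTI, with one arm 20% longer (mean 10.596 s).

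- Faster arm: σ² = ln(1 + (4.07/8.83)²) = 0.1926, so σ = 0.439; μ = ln 8.83 − 0.1926/2 = 2.082.
- 90th percentile of the faster arm: exp(2.082 + 1.2816 × 0.439) = 14.07 s.
- Let p be an arm's share above 14.07 s and E that share's contribution to the mean. If a fraction f of those cases is dropped, the retained mean is (mean − f·E)/(1 − f·p).

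With f = 0.5:

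| Arm | p | E (s) | Share dropped | Retained mean (s) |
|---|---|---|---|---|
| Faster | 10.0% | 1.763 | 5.0% | (8.83 − 0.882)/0.950 = 8.37 |
| Slower, SD also 20% larger | 19.3% | 3.545 | 9.7% | (10.596 − 1.773)/0.903 = 9.77 |
| Slower, SD 4.07 s | 17.1% | 2.978 | 8.5% | (10.596 − 1.489)/0.915 = 9.96 |

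The difference becomes 9.77 − 8.37 = 1.40 s, or 9.96 − 8.37 = 1.59 s with equal SDs. The first case removes about 9 of 180 and 17 of 180 patients.

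**4. A smoother model.** Take the same lognormal arms, with SD scaling with the mean and 10% disagreement overall, and let the log-odds of disagreement rise with each second of TTI:

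| Slope per second | Observed difference (s) |
|---|---|
| 0 | 1.77 |
| 0.1 | 1.63 |
| 0.2 | 1.46 |
| 0.4 | 1.24 |

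At slope 0.2 the exclusions are 8.2% against 11.8%. At slope 0 there is no bias.

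**The case against.** **The rules can be reconciled.** Analysing a mean presupposes that small differences between readers are kept, and exclusion could be meant only for disputes left unsettled by the third person, or only for the per-protocol set. These are reasonable intentions, but none is written. The exclusion sentence refers to the final analysis without qualification. What stands is that not every small timing difference should be read as a conflict.

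**The bias is not established.** A reader might infer that the rule does pull the TTI difference towards zero. The documents do not support that: they give neither a disagreement rate nor any link between disagreement and TTI. Other rules also already remove many messy cases, including grip changes, laryngeal pressure after the tube is held, airway adjuncts and consultant take-over. The conflict sentence therefore adds less than it might seem, and the illustration ignores this overlap. More extreme versions need heavy losses: dropping every case above the cut gives about 0.89 s, but only by removing 10% of one arm and 19% of the other.

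**Readers choosing a rule by arm.** A reader might also infer that assessors can see the grip and so keep or drop patients knowingly. The article states that assessors are blinded to group. Whether that holds on video is a separate question, and this point does not rest on it.

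**Table position.** A second contradiction is tempting here. Eligibility criteria {10} lists among exclusions "Procedures where the trainee deviates from the methodology, improper table position, CL grade found > 2", while Position says that where the table is not exact on video but "the intubator has declared a CL grade 1 or 2 view, the procedure will be considered adequate". The latter can be read as a tolerance that defines what is not improper. A cross-reference would help, but it is secondary and not part of this finding.

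**Conclusion.** The contradiction holds as written. It concerns the primary endpoint and decides which randomized patients are analysed. That article space is limited does not excuse it, because both rules are printed.

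The direction of harm is conditional: attenuation if longer intubations are disputed more often, loss of precision alone if disagreement is unrelated to TTI. The magnitude is unknown. The drop from 1.77 s to about 1.4 s (about 1.6 s with equal SDs) shows what a 5% against roughly 10% loss from the slow tail could do. It rests on an assumed lognormal shape, the pilot mean and SD, a true 20% difference and an assumed dispute pattern; it is not a forecast. Whether 149 per group is itself correct does not affect this conclusion.

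**What to change.** 1. Delete the conflict-exclusion sentence from Dropout criteria.
2. Keep the rule in Outcomes {12}: the mean of the two readers, with the third person already provided for settling disputes on time or method. State that this person is blinded to group, as the assessors are.
3. Define a dispute over time by a tolerance in seconds, chosen and justified by the investigators, and say how the adjudicated value enters the mean. The trial is under way and an interim analysis is planned after 120 cases, so fix this before any further comparison by arm.
4. Retain all patients with disputed videos in the primary analysis. Exclude them only in a sensitivity analysis, and report the number of disputed videos by arm.
5. Send any video already set aside for conflict to the third person; the recordings are stored.

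The cost is wording, adjudication that the plan already provides for, and one additional analysis. No new patients or data collection are needed.
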